##### **Postoperative respiratory rehabilitation (during hospitalization)**

- Sputum clearance and cough instruction
- Early mobilization
- Range-of-motion exercises for upper and lower extremities
- Strength training (trunk and limbs)
- Whole-body endurance exercise
- EMT will not be performed until 6 months postoperatively.

### **6.3 Data Source / Database**

Clinical records stored in the electronic medical record system.

### **6.4 Data to be Collected**

The following information will be obtained from medical records:

#### **6.4.1 Demographics and Clinical Information**

- Age (date of birth), height, weight, body mass index
- Past medical history, comorbidities, allergies (presence and details)
- Diagnosis information (diagnosis and date), clinical stage, clinical outcomes, treatment details
- Medication types

#### **6.4.2 Imaging Examinations**

- Videofluoroscopic swallowing study (VFSS)
- Whole-body CT (non-contrast and contrast-enhanced), chest radiography, transthoracic echocardiography
- Results and findings from the above examinations will be used

#### **6.4.3 Pulmonary Function Testing**

- Vital capacity, forced vital capacity, FEV1, diffusing capacity (DLCO)
- Results from the above tests will be used

#### **6.4.4 VFSS**

VFSS findings and results obtained at the start of neoadjuvant therapy and postoperatively will be used.

## **6.5 Endpoints and Assessments**

### **6.5.1 Primary Endpoint**

PAS score on videofluoroscopic swallowing study (VFSS).

#### **Rationale**

The PAS score obtained from VFSS is considered one of the most accurate and globally used methods for evaluating swallowing function.

PAS score definitions:

- 1: Material does not enter the airway.
- 2: Material enters the airway, remains above the vocal folds, and is ejected from the airway.
- 3: Material enters the airway, remains above the vocal folds, and is not ejected.
- 4: Material enters the airway, contacts the vocal folds, and is ejected.
- 5: Material enters the airway, contacts the vocal folds, and is not ejected.
- 6: Material passes below the vocal folds, and no subglottic residue is visible.
- 7: Material passes below the vocal folds; patient responds (cough), but residue remains.
- 8: Material passes below the vocal folds; no patient response; residue remains.

PAS  $\geq 3$  is regarded as dysphagia, and PAS  $\geq 6$  indicates aspiration.

### **6.5.2 Secondary Endpoints**

- Repetitive Saliva Swallowing Test (RSST)
- Functional Oral Intake Scale (FOIS)
- Maximum tongue pressure
- Ultrasound measures: laryngeal elevation distance; suprahyoid muscle cross-sectional area

#### **Rationale**

RSST, tongue pressure measurement, and ultrasound assessment of swallowing and respiratory muscles are non-invasive. RSST is widely used as a swallowing screening measure and can be administered by allied health professionals. Preoperative tongue pressure in esophageal cancer patients has been reported to be associated with the proportion of patients with PAS  $\geq 6$  on postoperative VFSS. Preoperative ultrasound-derived laryngeal elevation distance and suprahyoid muscle area have also been reported to relate to postoperative swallowing function. Ultrasound assessment of sternocleidomastoid and diaphragm motion is included to evaluate direct effects of EMT on respiratory muscles. These measures are considered important for interpreting the effect of EMT on swallowing.

### **6.5.3 Assessment Methods**

#### **Respiratory muscle strength**

Maximum inspiratory pressure (MIP) and maximum expiratory pressure (MEP) will be measured using the IOP-01 device. MIP is measured by a rapid maximal inspiration from end-expiration; MEP by a rapid maximal expiration from full inspiration. Participants sustain the pressure for  $\geq 2$

seconds; the maximum value during the hold is recorded. MIP is measured three times, with confirmation that variability is within 10%; the best value is used. Maximal phonation time is also measured by instructing participants to sustain phonation as long as possible after maximal inspiration. All measures are performed in a seated position.

### **Swallowing screening tests**

Swallowing screening tests include RSST, FOIS, and EAT-10. Assessments will be performed by a co-investigator speech-language-hearing therapist who is blinded to group allocation.

### **Repetitive Saliva Swallowing Test (RSST)**

After moistening the oral cavity, the number of saliva swallows completed in 30 seconds is observed. The assessor palpates the hyoid bone with the index finger and the thyroid cartilage with the middle finger and counts a swallow only when the thyroid cartilage clearly elevates past the palpating finger. Fewer than three swallows in 30 seconds is considered indicative of dysphagia on screening.

### **Functional Oral Intake Scale (FOIS)**

FOIS evaluates oral intake status on a 7-level scale from Level 1 (nothing by mouth) to Level 7 (total oral diet with no restrictions):

Level 1: Tube dependent, no oral intake.

Level 2: Tube dependent with minimal/inconsistent oral intake.

Level 3: Tube supplements with consistent oral intake.

Level 4: Total oral diet of a single consistency.

Level 5: Total oral diet with multiple consistencies requiring special preparation/compensations.

Level 6: Total oral diet with multiple consistencies without special preparation, but with specific limitations.

Level 7: Total oral diet with no restrictions.

### **Eating Assessment Tool-10 (EAT-10)**

EAT-10 is a 10-item questionnaire developed by Belafsky et al. (2008) for dysphagia screening. Each item is rated on a 5-point scale (0=no problem to 4=severe problem). A total score  $\geq 3$  suggests swallowing difficulty.

## **Tongue pressure**

Maximum tongue pressure (MTP) will be measured using a balloon-type tongue pressure device (JMS Tongue Pressure Measurement Device®, JMS, Hiroshima, Japan). The balloon is inflated to a baseline pressure of 19.6 kPa. In a seated position, the participant places the balloon against the anterior palate with lips closed, then presses the balloon upward maximally with the tongue for 7 seconds. The test is repeated three times; variability within 10% is confirmed, and the highest value is recorded as MTP.

## **Ultrasound: laryngeal elevation distance and suprahyoid muscle area**

Laryngeal/hyoid elevation distance will be assessed in a seated position using a 3.5 MHz convex probe applied to the submental region with ultrasound gel, avoiding compression of soft tissue. After confirming a mid-sagittal view and the ability to swallow saliva with the probe in place, a resting image is recorded, followed by video recording during spontaneous saliva swallowing. Stored images will be reviewed frame-by-frame (30 frames/s) to identify rest and maximal elevation positions, which are saved as still images. Hyoid displacement distance is then calculated using ImageJ. The displacement is quantified using the rest position (X0,Y0) as origin and maximal elevation (X1,Y1) as the measurement point with cranio-caudal movement as the x-axis and antero-posterior movement as the y-axis. Measurements are repeated three times; the maximum value (with  $\leq 10\%$  variability) is used.

Suprahyoid muscle cross-sectional area will be measured following Macrae et al. A 3.5 MHz convex probe is placed sagittally along the midline of the floor of the mouth at a level that visualizes both the hyoid bone and mandible with acoustic shadowing and the attached geniohyoid muscle. After spontaneous saliva swallowing, still images are saved and the area is calculated by manual tracing in ImageJ.

## **Appendicular skeletal muscle mass**

To verify that whole-body skeletal muscle mass and sarcopenia status do not differ between groups at baseline, appendicular skeletal muscle mass will be measured using seca mBCA 525. After measuring height and weight, participants (without socks/stockings) lie supine on a bed. Electrode pads are placed on the dorsum of both hands and feet and connected to the measurement mat positioned near the knees. Measurement is performed at rest for approximately 30 seconds. The appendicular skeletal muscle index is calculated as appendicular skeletal muscle mass divided by body surface area ( $m^2$ ) and will be used in statistical analyses.

## **Exercise capacity**

Exercise capacity is associated with PPCs after upper abdominal surgery. It will be assessed to confirm there is no between-group difference at baseline and preoperatively. Either cardiopulmonary exercise testing (CPET) with a cycle ergometer or the 6-minute walk test (6MWT) will be performed.

CPET: Using an expiratory gas analyzer (Minato), a ramp protocol is applied to safely evaluate

exercise capacity, aiming for termination within 8–12 minutes. After 1 minute rest and 1 minute warm-up at 0 W, participants maintain ~50 rpm, then workload increases by 20 W each minute until symptom limitation (dyspnea, leg fatigue) or inability to maintain cadence (<50 rpm). Expected homeostatic changes (e.g., increased breathing and heart rate) should resolve quickly with appropriate rest/hydration.

6MWT: Conducted according to the standard manual. Participants walk as far as possible in 6 minutes at a self-selected pace on a 30 m course (out-and-back) or track. Rest is allowed if needed, and the test may resume after recovery. The total distance walked in 6 minutes is recorded. The test is stopped immediately if SpO2 falls below 75%.

### Assessments performed within routine clinical care

- Respiratory muscle strength measurement
- Swallowing screening tests
- Tongue pressure measurement
- Appendicular skeletal muscle mass measurement
- Exercise capacity assessment

### Assessments performed specifically for this study

- Ultrasound assessment of swallowing muscles (laryngeal elevation distance and suprahyoid muscle area)

## 6.6 Schedule

Preoperative rehabilitation involves instruction, setting, and load adjustment of sham EMT (control) or EMT (intervention). Both groups receive breathing and cough instruction on the day before surgery. Postoperative rehabilitation follows the standard program without EMT; postoperative rehabilitation is routine care as previously practiced, whereas preoperative rehabilitation is performed for this study.

### 6.6.1 Assessment Schedule

| Assessment                            | Baseline
(1–2
days
before
surgery?) | Start of
neoadjuvant
therapy | Preoperative | Post-
op day
10 $\pm$ 4 | Post-
op 1
mo $\pm$ 7
d | Post-
op 3
mo $\pm$ 7
d | Post-
op 6
mo $\pm$ 7
d |
|---------------------------------------|-------------------------------------------------|------------------------------------|--------------|-------------------------------|----------------------------------|----------------------------------|----------------------------------|
| Informed
consent                   | —                                               | •                                  | —            | —                             | —                                | —                                | —                                |
| Respiratory
muscle
strength*1   | —                                               | •                                  | •            | $\Delta$ *2                   | •                                | •                                | •                                |
| Swallowing
screening*1             | —                                               | •                                  | •            | $\Delta$ *2                   | •                                | •                                | •                                |
| Tongue
pressure*1                  | •                                               | •                                  | •            | •                             | •                                | •                                | •                                |
| Ultrasound
swallowing
muscles*1 | •                                               | •                                  | •            | •                             | •                                | •                                | •                                |

|                                   |   |   |   |     |     |     |     |
|-----------------------------------|---|---|---|-----|-----|-----|-----|
| Appendicular skeletal muscle mass | ● | ● | — | ●   | ●   | ●   | ●   |
| Exercise capacity                 | ● | ● | — | △*2 | △*2 | △*2 | △*2 |

\*1 Assessments are performed by research staff blinded to participant allocation.

\*2 Performed only when approved by the attending physician.

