#### Rationale for sample size

Assuming EMT improves PAS score, and referring to Zhang et al., the mean difference in PAS score between groups is set to 0.8 with a common standard deviation of 0.8. With  $\alpha=0.05$  (two-sided), power=0.80, and allocation ratio 1:1, R-based calculation yields 16 participants per group (32 total). Accounting for dropouts (~5% in prior work) and exclusion of patients with postoperative recurrent laryngeal nerve palsy (approximately 10% since 2020), the minimum target sample size is set to 40.

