### 8.2 Statistical Analysis

Patients with postoperative recurrent laryngeal nerve palsy will be excluded from analyses. Between-group comparisons will use t-tests for continuous variables and Fisher's exact test or chi-square tests for categorical variables. Statistical significance will be set at  $P<0.05$ .

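### Day-10 FOIS sits behind an unspecified physician-approval condition it does not need, so the worst scores at that visit may be under-recorded

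*Protocol*

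**What the plan says.** Protocol 6.5.2 lists RSST and FOIS among the secondary endpoints and names no visit for either. The swallowing screening paragraph in 6.5.3 defines the package: "Swallowing screening tests include RSST, FOIS, and EAT-10". It assigns the package to a speech-language-hearing therapist who does not know the allocation.

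In the table in 6.6.1, the day 10±4 cell of the swallowing screening row is marked with a triangle and note 2: "Performed only when approved by the attending physician". The same row is unconditional at the start of neoadjuvant therapy, preoperatively, and at 1, 3 and 6 months. Note 2 also applies to respiratory muscle strength at day 10 and to exercise capacity at every postoperative visit. Tongue pressure and swallowing-muscle ultrasound are unconditional at day 10. The protocol does not say on what grounds approval is given or withheld.

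The FOIS definition in 6.5.3 begins with "Level 1: Tube dependent, no oral intake", so a patient who is not eating has a valid score, the lowest on the scale.

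**The concern.** FOIS describes what a patient is currently eating and asks for no effort or swallow. It is conditional at day 10 only because it shares a row with RSST, which does ask the patient to swallow repeatedly. Withholding a swallowing assessment is a clinical judgement about the patient, and poor swallowing or poor general condition are plausible grounds for it. If those grounds apply, the patients left without a FOIS rating will tend to be those at its lowest levels, and whether a score exists will depend on the score itself.

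Day 10 is the first postoperative visit and the one closest to an intervention given only before surgery, so a comparison there would be of natural interest. Section 6.2.4 blinds participants and outcome assessors. It does not mention attending physicians, who decide on approval, so unequal approval between the arms is not excluded.

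This is a collection rule in the protocol. A statistical analysis plan can say how to treat a missing score, but it cannot recover a rating that was never made.

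**Working it through.** **Plan's own figure.** The protocol gives no day-10 FOIS distribution and no approval rate, so there is no stated figure on this point to reproduce. The sample size in 8.1 is for PAS (difference 0.8, SD 0.8, two-sided 0.05, power 0.80). By the normal approximation, 2 × (1.96 + 0.84)² × (0.8/0.8)² = 15.7, rounded up to the stated 16 per group. No FOIS quantity enters it.

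**What the gate covers at day 10±4.**

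| Measure | What the patient must do | Day 10 status |
|---|---|---|
| Tongue pressure | three maximal presses of 7 seconds | unconditional |
| Ultrasound | saliva swallow under the probe | unconditional |
| RSST | repeated saliva swallows over 30 seconds | approval needed |
| FOIS | nothing; intake status is rated | approval needed |

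The least demanding of the four is gated, while two that need active effort are not.

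**Illustration; every rate here is assumed.** Let p be the share of an arm at Level 1 and u the fraction of those patients left unassessed. Put everyone else at Level 5 and assessed.

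- True arm mean = 5(1 − p) + 1·p = 5 − 4p
- Observed arm mean = [5(1 − p) + p(1 − u)] / (1 − pu)

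With p = 0.25 (control) and 0.10 (EMT):

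- True: control 5 − 1.00 = 4.00; EMT 5 − 0.40 = 4.60; difference 0.60.
- u = 0.5: control (3.75 + 0.125)/0.875 = 4.43; EMT (4.50 + 0.05)/0.95 = 4.79; difference 0.36, so 40% of the effect is lost.
- u = 1: control 5; EMT 5; difference 0.

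Range over other assumed shares, with 20 per arm:

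| Level 1, control / EMT | True difference | u = 0.5 | u = 1 | Scores missing at u = 1 (of 40) |
|---|---|---|---|---|
| 10% / 5% | 0.20 | 0.11 | 0 | 3 |
| 15% / 5% | 0.40 | 0.22 | 0 | 4 |
| 25% / 10% | 0.60 | 0.36 | 0 | 7 |
| 30% / 15% | 0.60 | 0.38 | 0 | 9 |
| 15% / 15% | 0 | 0 | 0 | 6 |
| 30% / 30% | 0 | 0 | 0 | 12 |

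In the last two rows the contrast is unbiased, but at u = 1 both arm means are too high, by 5 − 4.4 = 0.6 and 5 − 3.8 = 1.2 levels.

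**Unequal approval.** Take 15% at Level 1 in both arms, so the true difference is 0. If all of these patients go unassessed in the control arm and none in the EMT arm, the observed difference is 4.4 − 5 = −0.6. With the arms reversed it is +0.6. The sign is therefore not fixed.

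**The case against.** The mechanism is inferred. Note 2 gives no criterion and does not mention oral intake. It also governs respiratory muscle strength and exercise capacity, so it can be read as a general check of fitness for testing. Ultrasound during a saliva swallow is ungated at the same visit, so the gate does not simply follow swallowing status. This stands. A reader might infer that the rule removes the lowest FOIS levels, or that non-eating patients are missing precisely when they score worst. The document supports only that they may be.

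A reader might also infer that a planned day-10 analysis is biased towards no effect. Section 8.2 says only "Between-group comparisons will use t-tests for continuous variables and Fisher's exact test or chi-square tests for categorical variables". It names no visit and no FOIS test, and 8.3.1 defines outcomes for PAS alone. The bias arises only if day-10 FOIS is compared, and the working shows that its direction is not determined.

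The zero in the illustration follows from its assumptions, since all assessed patients other than those at Level 1 are placed at Level 5 in both arms. If those patients also differed between arms, that part of the difference would remain visible. The figures show what the rule could do and are not an estimate for this trial.

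Finally, how to analyse missing RSST scores, for example by ranking them as worst, is a debatable choice that belongs to an analysis plan not shown here. Its absence is no finding, and no such rule is proposed.

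None of this explains why a rating with a defined value for the non-eating patient should need approval.

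**Conclusion.** The point holds in limited form. At day 10±4 a listed secondary endpoint that can be scored for every patient is collected only at the attending physician's discretion, with no stated criterion. Followed as written, this may under-record low FOIS scores at that visit and could bias any comparison made there.

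Its size cannot be determined from the protocol. Under the assumed scenarios with unequal Level 1 shares, a true difference of 0.20 to 0.60 levels shrinks to between 0.11 and 0.38 when half of the Level 1 patients are unassessed, and to 0 when all are. With equal shares and equal approval there is no bias in the contrast. With unequal approval the error can go either way. If approval is unrelated to intake status, the loss is one of numbers only.

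The scope is one visit and secondary endpoints. Screening at 1, 3 and 6 months is already unconditional. A reader might carry the concern over to the main result, but the primary endpoint, PAS on VFSS, is not in the gated row, and neither it nor the sample size is affected by this note.

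**What to change.** In 6.6.1, take FOIS out of the swallowing screening row and give it a row of its own. Mark it unconditional at day 10±4, as it already is at the other visits, and state that the blinded therapist named in 6.5.3 rates it for all patients from intake status. Leave the approval condition on RSST as it stands, and add that the reason is recorded whenever RSST is not approved.

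The cost is one table row, one sentence and one field on the case record. It needs no new procedure or staff and changes nothing in patient management.

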### 6.6.2 Study Period

Overall study period: From institutional authorization date to March 31, 2030.

Data accumulation / enrollment period: From institutional authorization date to March 31, 2029.

Analysis period: April 1, 2029 to June 30, 2029.

## **7.0 Study Initiation, Amendments, and Completion**

### **7.1 Initiation**

Before starting the study, the Principal Investigator will submit a new application using the designated institutional forms (Kindai Forms 1 and 2), together with the Study Implementation Plan, participant information and consent documents, and consent form. The study will begin after review and approval by the Ethics Committee and authorization by the Dean of the Faculty of Medicine.

### **7.2 Amendments**

If changes or revisions are needed, the Principal Investigator will submit an amendment application using the designated form (Kindai Form 4). Changes will be implemented after Ethics Committee review/approval and institutional authorization by the Dean.

### **7.3 Completion**

Upon completion, discontinuation, or suspension of the study, the Principal Investigator will promptly report to the Dean using the designated form (Kindai Form 6). The study will be discontinued if the Ethics Committee recommends or instructs cessation.

## 8.0 Statistical Considerations

### 8.1 Target Sample Size

Control (Sham EMT): 20 participants; EMT: 20 participants; total: 40 participants.

#### Rationale for sample size

Assuming EMT improves PAS score, and referring to Zhang et al., the mean difference in PAS score between groups is set to 0.8 with a common standard deviation of 0.8. With  $\alpha=0.05$  (two-sided), power=0.80, and allocation ratio 1:1, R-based calculation yields 16 participants per group (32 total). Accounting for dropouts (~5% in prior work) and exclusion of patients with postoperative recurrent laryngeal nerve palsy (approximately 10% since 2020), the minimum target sample size is set to 40.

### 8.2 Statistical Analysis

Patients with postoperative recurrent laryngeal nerve palsy will be excluded from analyses. Between-group comparisons will use t-tests for continuous variables and Fisher's exact test or chi-square tests for categorical variables. Statistical significance will be set at  $P<0.05$ .

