## 4.0 Background and Rationale

Esophagectomy with reconstruction is a highly invasive curative treatment for esophageal cancer. Surgery-related complications after esophagectomy include pulmonary complications, anastomotic leakage, anastomotic stricture, recurrent laryngeal nerve palsy, and dysphagia. In our institutional data, the postoperative pneumonia rate decreased from 25.9% (through fiscal year 2019, predominantly open thoracotomy) to 18.0% (fiscal years 2020–2023, after transitioning to minimally invasive approaches), suggesting that postoperative pulmonary complications (PPCs) are declining with less invasive surgery (unpublished data). However, postoperative dysphagia after esophagectomy has remained relatively constant at approximately 15% in our data from fiscal years 2016–2023 (unpublished data).

Prior research in esophageal cancer patients undergoing esophagectomy has reported that recurrent laryngeal nerve palsy (OR 6.6, 95% CI 1.30–33.8) and preoperative CT-measured suprahyoid/geniohyoid muscle cross-sectional area (OR 3.6, 95% CI 1.16–11.1) are significant predictors of postoperative dysphagia. In addition, preoperative tongue pressure, an index of suprahyoid and swallowing-muscle strength, has been reported as a predictor of aspiration pneumonia after esophagectomy. Furthermore, laryngeal elevation is known to significantly influence swallowing after esophagectomy, and reduced laryngeal elevation distance on postoperative videofluoroscopic swallowing studies has been associated with aspiration.

Expiratory muscle training (EMT), which applies expiratory resistance during exhalation, has been investigated as an intervention for dysphagia. Because EMT induces activity in orofacial and pharyngeal muscles (e.g., submandibular, palatal, lingual, and pharyngeal muscles), it may improve muscle strength and cross-sectional area, contribute to the coordination of bolus transport, maintain swallowing safety and efficiency, and lead to functional improvement. A meta-analysis of randomized controlled trials in stroke patients reported that EMT improved the PAS score by  $-0.81$  (95% CI  $-1.19$  to  $-0.43$ ;  $I^2=39\%$ ;  $P<0.0001$ ). EMT is believed to enhance muscular and neural adaptations relevant to swallowing recovery, with direct effects in reducing aspiration and pharyngeal residue.

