#### **6.2.4 Randomization and Allocation**

This study is conducted as part of routine preoperative respiratory rehabilitation under health insurance; participants will perform either sham EMT (control) or EMT (intervention) as a component of the rehabilitation program. After obtaining consent, participants will be randomly assigned using the UMIN medical research support (case registration and allocation) system, cloud version [INDICE cloud]. Allocation factors are: age (<65, ≥65), sex (male/female), and baseline PAS score category: 1–2 (no dysphagia), 3–5 (dysphagia), 6–8 (aspiration). Allocation will be performed using a non-deterministic minimization method. These factors are based on reports indicating associations of age and sex with swallowing function, and to balance baseline swallowing function between groups. The INDICE cloud randomization program will be prepared with data-management support from KHGRAC and managed strictly to prevent external disclosure. Participants and outcome assessors will be blinded to allocation.

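### Section 8.2 drops patients with postoperative recurrent laryngeal nerve palsy from every analysis, which selects on a prognostic event that is known only after randomisation and surgery

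*Protocol*

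**What the plan says.** The Protocol, section 8.2, gives the rule in one sentence: "Patients with postoperative recurrent laryngeal nerve palsy will be excluded from analyses". It is not confined to one endpoint or to a secondary analysis set, and the protocol names no analysis of all randomised patients beside it.

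The rule is deliberate. The sample size rationale in 8.1 allows for "exclusion of patients with postoperative recurrent laryngeal nerve palsy (approximately 10% since 2020"), next to a dropout allowance of about 5%.

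On timing, section 6.2.4 says: "After obtaining consent, participants will be randomly assigned using the UMIN medical research support (case registration and allocation) system". The schedule in 6.6.1 places consent at the start of neoadjuvant therapy. Allocation therefore precedes the training period and the operation.

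On prognosis, section 4.0 lists two significant predictors of dysphagia after esophagectomy. One is "recurrent laryngeal nerve palsy (OR 6.6, 95% CI 1.30–33.8"); the other is a preoperative muscle measure with OR 3.6 (95% CI 1.16 to 11.1).

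On the target population, objective (1) in 5.0 concerns patients scheduled for esophagectomy with reconstruction and makes no reference to palsy. Objective (2) carries the estimated effect on aspiration forward to the design of a multicentre study.

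**The concern.** Randomisation makes the two arms comparable as allocated. Removing patients because of something that happens later keeps that comparability only if the event, and its detection, do not depend on the arm. Here the event is observed in the same postoperative period as the swallowing outcome and is associated with that outcome.

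Section 6.2.4 blinds participants and outcome assessors. Nothing says who labels a patient as having palsy, on what criteria, or whether that person knows the allocation. Neither the data items in 6.4 nor the schedule in 6.6.1 has an entry for diagnosing palsy. If palsy were looked for mainly in patients who cough or aspirate, and EMT changed those symptoms, exclusion would depend on treatment.

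A second problem remains even if there is no bias. EMT is given before surgery, when nobody knows who will develop palsy. An effect estimated only in palsy-free patients describes a group that cannot be selected at the time of prescription. Objective (1) would be answered for a different population from the one it names, and the planning figure in objective (2) would carry the same restriction.

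**Working it through.** **1. The plan's own sample size.** Inputs from 8.1: "the mean difference in PAS score between groups is set to 0.8 with a common standard deviation of 0.8", two-sided alpha 0.05, and "power=0.80, and allocation ratio 1:1, R-based calculation yields 16 participants per group (32 total").

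- Normal approximation: n = 2 × (1.960 + 0.842)² × 0.8² / 0.8² = 15.7, so 16 per group. The stated figure is reproduced.
- The exact t-test needs 16.7, so 17 per group (34 in total).
- Inflation for 5% dropout and 10% palsy: 32 / (0.95 × 0.90) = 37.4, so 38; 34 / (0.95 × 0.90) = 39.8, so 40. The target of 40 covers both.

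**2. Share of dysphagia cases that the rule removes.** Inputs: palsy 10% (8.1), OR 6.6 (4.0), and from 4.0 "postoperative dysphagia after esophagectomy has remained relatively constant at approximately 15% in our data from fiscal years 2016–2023". Let p1 be the dysphagia risk with palsy and p0 the risk without:

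- 0.10 × p1 + 0.90 × p0 = 0.15
- p1/(1 − p1) = 6.6 × p0/(1 − p0)

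The solution is p0 = 0.115 and p1 = 0.462. Check: 0.10 × 0.4624 + 0.90 × 0.1153 = 0.150.

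Share of cases in palsy patients = 0.10 × 0.4624 / 0.15 = 0.308, or about 31%. Among 40 patients that is 40 × 0.10 × 0.4624 = 1.85 of the 40 × 0.15 = 6 expected cases.

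| OR | Palsy | Dysphagia | Share removed |
|---|---|---|---|
| 1.30 (lower limit) | 10% | 15% | 12% |
| 6.6 | 10% | 15% | 31% |
| 33.8 (upper limit) | 10% | 15% | 50% |
| 6.6 | 5% to 15% (assumed) | 15% | 17% to 43% |
| 6.6 | 10% | 10% to 20% (assumed) | 34% to 28% |

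**3. What remains evaluable out of 40.**

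- Current rule: 40 × 0.95 × 0.90 = 34.2, about 17 per arm.
- Without the exclusion: 40 × 0.95 = 38, or 19 per arm.

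**4. Power at a difference of 0.8, two-sided t-test.** The SDs above 0.8 are assumptions, because the protocol gives no SD for a population that includes palsy.

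| Evaluable per arm | SD | Power |
|---|---|---|
| 17 (current rule) | 0.8 | 0.81 |
| 19 | 0.8 | 0.85 |
| 19 | 0.85 | 0.81 |
| 19 | 1.0 | 0.67 |

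The two extra patients per arm are offset once the SD reaches about 0.85.

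**The case against.** The strongest defence is that palsy follows from the operation, not from preoperative breathing exercises. Nothing in the protocol suggests that EMT changes palsy risk. If palsy and its diagnosis are independent of arm, the palsy-free comparison is unbiased for palsy-free patients. The exclusion is also prespecified, is allowed for in the sample size, and should affect only about two patients per arm. This stands as far as it goes: it rules out calling the result biased. It does not answer the mismatch with the objective, and its premise about diagnosis is not secured by the text.

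A reader might infer more than the protocol supports:

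- **That symptom-driven labelling will occur.** The protocol is silent on how palsy is diagnosed. Routine practice or a separate analysis plan may settle it. This is a possibility, not a finding.
- **That palsy is the strongest predictor.** Section 4.0 calls it significant and does not rank it. Its interval overlaps heavily with that of the muscle measure.
- **That a third of the trial's events will certainly be lost.** The 31% applies an OR from a cited study to institutional rates from different periods (dysphagia 2016–2023, palsy since 2020). The criterion behind the 15% is not given, so it cannot be equated with PAS ≥3 or ≥6. The primary endpoint is sized as a mean difference, so this share does not determine primary power.
- **That keeping palsy patients raises power.** This holds only if the SD stays near 0.8, and patients at higher risk of poor PAS scores may well widen it.
- **That the 10% allowance in 8.1 can be removed and the target cut.** That would lower the number just when the variance may rise.

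**Conclusion.** The point holds and should be corrected before analysis. As written, 8.2 makes a post-randomisation, prognostic exclusion apply to every analysis, with no all-randomised comparison beside it. The protection of randomisation is given up, and the estimate refers to a population other than the one in 5.0. Neither conclusion depends on any calculation.

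The size of the loss is less certain: about 31% of dysphagia cases at the protocol's point estimates, and 12% to 50% over the OR's interval. It assumes that the cited OR applies to this hospital's patients and that the 10% and 15% rates describe the same population.

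The documents do not show that the treatment effect would be biased, or in which direction.

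**What to change.** Replace the exclusion sentence in 8.2 with wording such as: *The primary analysis includes all randomised patients who have a postoperative PAS, in the arm assigned, regardless of recurrent laryngeal nerve palsy. An analysis without patients with palsy is a sensitivity analysis. The frequency of palsy is reported by arm.*

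Keep the target of 40 and restate its rationale in 8.1: about 19 evaluable per arm after 5% dropout, with power at a difference of 0.8 shown over a range of SDs (0.85 at SD 0.8, about 0.81 at 0.85, about 0.67 at 1.0). State that the values above 0.8 are assumptions.

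The cost is an amendment to 8.1 and 8.2, with no additional patients. The drawback is that including palsy patients may widen the PAS SD and lower the stated power, so the amendment should not claim a power gain. The palsy-free result remains available as the sensitivity analysis.
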